### Data management

All documents and source documents will be stored in the data center. These documents include informed consent, all reports, administrative forms, copies of medical records, and other identifiable patient material. In the data center, data will be stored in file cabinets locked to areas with limited access, thus keeping participants anonymous. All electronic participant data will be deposited in our department’s relevant platform. The principal investigator will have access to the final data sets and be responsible for the data. After application and permission, related researchers can have access to the anonymous data for future studies. Additionally, we will deliver a completely deidentified data set to an appropriate data archive for sharing purposes.

### Statistical analysis

The analyses will be based on the intention-to-treat (ITT) principle in accordance with the Consolidated Standards of Reporting Trials (CONSORT). Statistical analyses will be performed with SAS version 9.2 (SAS Institute, Cary, North Carolina). Data will be presented as the mean ± standard deviation or median and interquartile range depending on their distribution. Categorical data, including the primary outcome, will be analyzed using the chi-square test between two groups. Continuous data will be analyzed using Student’s *t* test or the Mann-Whitney test as appropriate. The effect of HC on the dichotomous outcomes will be assessed by multivariable logistic regression analysis including possible confounders, including birth weight and gestational age. Statistical results will be reported as point estimates and 95% confidence intervals.

Mid-term data analysis will be conducted after inclusion of the first 98 patients. The principal investigator will decide whether any measure should be taken in light of the results. Case report forms (CRFs) will be entered by two independent researchers to ensure accuracy.

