### Study design

This multicenter double-blind randomized controlled trial will be performed at three centers in China. The enrollment period will be 1 year, and there will be a series of follow-up for every child until 2 years corrected age, which is the revised age from the 40th gestation week for a premature baby. The human research ethics committees at each participating center approved the trial, and an independent academic board will monitor the trial.

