### Sample size calculation

According to the data from the participating centers in the past 2 years and the data presented from the range of previous studies [27–29], the incidence of early BPD in infants with gestational age 26^+0^ to 30^+6^ weeks was 68–77%, and 40% developed moderate or severe BPD. The effect of HC therapy was assumed to reduce moderate or severe BPD (the primary endpoint) to 25% or less (number needed to treat, NNT = 5). Adopting a maximum significance level of *α* = 0.05 and a minimum test power of 80%, the number of subjects per group will be *N* = 81, which will be increased by 20% to compensate for potential dropouts during the follow-up, leading to 98 subjects per group (total 98 × 2 = 196 subjects).

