### Randomization

Eligible patients will be randomized at day 28 after birth in each center after at least one guardian provides informed consent. A list of all eligible patients not included in the study will be provided from all centers throughout the time of enrollment. This trial will be protected from selection bias by using concealed, stratified, and blocked randomization. Randomization will be stratified according to gestational age stratum (26^+0^ to 28^+6^ weeks, and 29^+0^ to 30^+6^ weeks) in each study center. Multiple birth infants will be internally randomized. The randomization procedure will be generated by using Excel software by the GCP faculty at the participating hospitals, and it will be sealed in a sequentially numbered envelope to maintain the allocation concealment. According to the allocation sequence, drug packages will be hidden and labeled sequentially. Participants will receive packaged drug in the order of recruitment. The first dose of study medication will be administered within 1 h after randomization.

The complete random sequence will be kept by the primary researcher at the affiliated hospital of Southwest Medical University. Centers will individually have emergency envelopes that contain the treatment information for patients. Emergency envelopes can be unsealed only under special conditions.

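### The unstratified chi-square named for the primary outcome does not match randomisation by centre and gestational age with siblings randomised internally; it is probably conservative and gives up some power

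*Protocol article*

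**What the plan says.** **Design.** The Study design section says the trial "will be performed at three centers in China". The Randomization section says: "This trial will be protected from selection bias by using concealed, stratified, and blocked randomization". It continues: "Randomization will be stratified according to gestational age stratum", with two bands (26+0 to 28+6 and 29+0 to 30+6 weeks) applied in each centre. That makes 3 × 2 = 6 strata. On siblings it says only: "Multiple birth infants will be internally randomized".

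**Analysis.** The Statistical analysis section says: "Categorical data, including the primary outcome, will be analyzed using the chi-square test between two groups". It adds that the hydrocortisone effect on dichotomous outcomes will be assessed by "multivariable logistic regression analysis including possible confounders, including birth weight and gestational age". Neither centre nor family is named there, and no other section mentions correlation between siblings.

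**Error rate and size.** The Sample size calculation section sets a "maximum significance level of *α* = 0.05" without stating sidedness (two-sided is assumed below). It takes 40% moderate or severe BPD in controls and 25% or less on hydrocortisone, and plans 98 infants per group.

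**The concern.** Stratified, blocked randomisation forces the arms to be balanced on centre and gestational age. If those factors predict the outcome, the difference between arms varies less from trial to trial than under simple randomisation. The ordinary chi-square does not know this: its variance still contains the between-stratum part that the design has removed. The same happens when siblings with similar outcomes are placed in opposite arms.

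The result is a test with a true error rate below its nominal 5%, intervals wider than they need be, and lower power than the same data would support. The planned logistic model covers gestational age but does not name centre. The Use of cointervention section leaves respiratory support to each centre's own guidelines, and the primary outcome turns on respiratory support and oxygen need, so centre is plausibly prognostic too.

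**Working it through.** **1. Starting point: the crude test at the planned size.** Take p1 = 0.40, p2 = 0.25 and n = 98 per arm, so the pooled rate is 0.325.

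- Null standard error: √(2 × 0.325 × 0.675 / 98) = 0.0669.
- Alternative standard error: √((0.24 + 0.1875) / 98) = 0.0660.
- Power: Φ((0.15 − 1.96 × 0.0669) / 0.0660) = Φ(0.286) ≈ 61%.

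This is below the stated 80%. The stated rates need 152 per group, not 81; the 81 corresponds to 40% v 20%, which is what a number needed to treat of 5 implies. That is a separate and larger problem. It matters here only because the trial has little power to give away.

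**2. Strata: formula.** Let R² be the share of outcome variance explained by the strata. The true variance of the difference is then (1 − R²) times what the chi-square assumes, so

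true α = 2 × (1 − Φ(1.96 / √(1 − R²))), and intervals are too wide by a factor 1/√(1 − R²).

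The documents give no rates by gestational-age stratum. I assume two equal strata with overall control failure of 40%, so R² = (half the gap)² / (0.40 × 0.60).

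| Assumed control failure, younger/older | R² | True α | Interval too wide by |
|---|---|---|---|
| 40%/40% | 0 | 5.0% | 0% |
| 45%/35% | 0.05²/0.24 = 1.0% | 4.9% | 0.5% |
| 50%/30% | 0.10²/0.24 = 4.2% | 4.5% | 2.1% |
| 55%/25% | 0.15²/0.24 = 9.4% | 3.9% | 5.0% |
| 60%/20% | 0.20²/0.24 = 16.7% | 3.2% | 9.5% |

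**3. Strata: simulation.** Balanced allocation, 98 per arm in six strata (20, 20, 15, 15, 14 and 14 per arm), 20,000 to 40,000 trials per scenario. Power is at a within-stratum odds ratio of 0.5. That ratio turns 40% into 25%: odds 0.667 × 0.5 = 0.333.

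| Split | α, chi-square | α, CMH | Power, chi-square | Power, CMH |
|---|---|---|---|---|
| 50%/30% | 4.4% | 4.9% | 59% | 60% |
| 55%/25% | 3.9% | 5.1% | 54.8% | 58.2% |
| 60%/20% | 3.1% | 5.0% | 48.1% | 54.9% |

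The loss is about 1, 3 and 7 points. In a run that added differences between centres, α was 3.7% v 4.9% and power 52.6% v 57.2%.

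**4. Siblings.** Let f be the share of infants enrolled with a co-twin in the opposite arm, and ρ the correlation of their outcomes. There are f × n split pairs, and each pair's covariance reduces the variance of the difference, so the variance ratio is 1 − fρ. The documents give neither f nor ρ. Assumed values:

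- f = 0.2, ρ = 0.3: ratio 0.94, true α 4.3%.
- f = 0.3, ρ = 0.4: ratio 0.88, true α 3.7%.
- f = 0.4, ρ = 0.5: ratio 0.80, true α 2.8%.

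Siblings share a centre and usually a stratum. Where steps 2 and 4 are combined, ρ must therefore mean the correlation left after the strata. For example, R² = 10% with fρ = 0.3 × 0.3 = 0.09 gives a ratio of 0.81 and a true α of 2.9%.

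**The case against.** **The test is valid.** A crude analysis after stratified randomisation keeps the error at or below 5%, so no false-positive risk arises from the strata. This stands: the cost is power and precision.

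**The size is assumed.** No stratum rates, twin share or correlation appear in the documents. The 55%/25% and 60%/20% splits are odds ratios of 3.7 and 6. Eligibility already restricts the trial to infants with early BPD who are not invasively ventilated and have had no postnatal steroids, which may flatten the gestational-age gradient. Some co-twins will not qualify, which lowers f. This also stands, and it is why the range runs down to no loss. Still, a trial that stratifies on gestational age and lists it as a possible confounder evidently expects it to matter.

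**Covariate detail may sit elsewhere.** The confounder list is open-ended, and a fuller protocol or analysis plan may name centre and a sibling method. That answers a complaint about omission. It does not answer the mismatch in a rule that the article does state, namely which test is applied to the primary outcome.

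**Stronger readings that a reader might infer:**

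- *The error rate is inflated because siblings are treated as independent.* This needs siblings to share an arm; f = 0.3 and ρ = 0.4 would then give a ratio of 1.12 and 6.4%. The Randomization wording, though terse, points to randomisation within the sibling set and does not suggest a shared arm.
- *No primary analysis is designated.* The chi-square is the only test tied by name to the primary outcome, and the logistic sentence reads naturally as supporting adjustment. A clearer hierarchy would help, but it is not absent.
- *Unadjusted t or rank tests for continuous outcomes are an error.* They are valid in a randomised trial; covariate adjustment would be a gain in efficiency.

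**Conclusion.** The mismatch is real and lies in a stated rule: six randomisation strata and internally randomised multiples, followed by an unstratified test of the primary outcome and a supporting model that names neither centre nor family.

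The consequence is conservatism. It rests on the strata being prognostic and on a two-sided 5% test. The gestational-age splits in the working put the loss between about 1 and 7 points of power; with no prognostic value it is nil. The sibling contribution also needs the split-arm reading and a positive correlation, and its size cannot be fixed from the documents.

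This is a modest, inexpensive improvement that should be made. It does not threaten the validity of a positive result.

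**What to change.** Before unblinding, name one primary analysis of survival without moderate or severe BPD. Either of these would do:

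- CMH stratified by centre × gestational-age stratum; or
- logistic regression with arm, centre, gestational age and birth weight fixed in advance. That is five coefficients besides the intercept (three centres need two), against roughly 196 × 0.325 ≈ 64 failures at the planned rates.

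State that the crude chi-square is supportive. Account for siblings with family-clustered (GEE) standard errors, at least as a sensitivity analysis; CMH by stratum alone does not do this.

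**Cost.** No extra infants or visits are needed. Gestational age and birth weight are already collected, and centre is known from randomisation. The Clinical data collection section lists only singleton or multiple status, which does not link siblings, so a family identifier must be added to the case report form.

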### Use of cointervention

All randomized patients will be subjected to cointerventions, such as respiratory support and comedication, according to the guidelines and protocols of the participating centers. The participants will not be given other treatments outside of the trial interventions and cointerventions.

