### Clinical data collection

At the time of randomization, baseline data will be collected from all included patients, including maternal and patient characteristics. Demographic data will include sex, birth weight, gestational age, 5-min Apgar score, surfactant therapy, prenatal corticosteroid use, premature rupture of the membrane before the onset of labor (> 18 h), singleton/multiple birth, and mode of delivery. Population characteristics will be used to compare outcomes between the two groups.

The following clinical data will be collected: continuous positive airway pressure (CPAP)-assisted time, invasive ventilator-assisted time, days of hospitalization, days on supplemental oxygen, IVH, spontaneous intestinal perforation, NEC, and ROP.

During HC treatment, respiratory support, blood sugar, blood pressure, and anthropometric data will be collected. Outcome variables and cointerventions will be recorded at 36 weeks PMA.

After discharge, one trained investigator in each center will follow up all patients at 40 weeks PMA and at 12, 26, 52, and 104 weeks corrected age. We will provide free neurodevelopmental impairment examinations to promote follow-up rates. For potential dropouts during the follow-up, we will expand the sample size by 20% and the missing data will be ignored in the analysis. The outcomes at each time point mentioned above will be collected by the investigators (Table 1).

**Table 1 Tab1:** SPIRIT figure: showing time points for enrollment, interventions, and assessment

	Study period						
	Enrollment	Allocation	Post-allocation				Close-out
Time point	At 4 weeks after birth	At 4 weeks after birth	At 36 weeks postmenstrual age	At 40 weeks postmenstrual age	At 12, 26 weeks corrected age	At 52 weeks corrected age	At 104 weeks corrected age
Enrollment:							
Eligibility screen	X						
Informed consent	X						
Demographic data	X						
Allocation		X					
Intervention:							
Hydrocortisone		X					
Placebo		X					
Assessments:							
Baseline variables assessments	X	X					
Primary outcome			X				
Secondary outcomes:							
Brain volume				X			
Others			X				
Long-term outcomes:							
Neurodevelopmental impairment, hearing loss, and blindness							X
Number of readmissions						X	
Weight, length, and head circumference				X	X	X	X
Behavioral problems, premature birth-related mortality							X

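### The primary test ignores the centre and gestational-age strata used in randomization; it stays valid, but is conservative and loses some power if outcome rates differ between strata

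*Protocol article*

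**What the plan says.** - **Randomization.** "Randomization will be stratified according to gestational age stratum", with two strata, separately in each centre and in blocks. Study design gives three centres, so there are 3 × 2 = 6 strata.
- **Use of cointervention.** Respiratory support and other medication are given "according to the guidelines and protocols of the participating centers". Primary outcome defines success by respiratory support, inspired oxygen and saturation at 36 weeks.
- **Clinical data collection.** After discharge, "one trained investigator in each center will follow up all patients at 40 weeks PMA" and at the later visits up to 104 weeks corrected age.
- **Statistical analysis.** A two-group chi-square test is fixed for categorical data, and the primary outcome is expressly included. Continuous data get a t test or a Mann-Whitney test. The effect on dichotomous outcomes is also "assessed by multivariable logistic regression analysis including possible confounders, including birth weight and gestational age". Centre is named in none of these.

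**The concern.** Blocking within strata removes chance imbalance between arms on the stratifying factors. The between-strata part of the outcome variance therefore no longer contributes to the error of the treatment comparison. An unstratified test still counts it, so the stated standard error is larger than the real one whenever strata differ in outcome rate.

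Differences between centres are plausible here, because local respiratory practice feeds into an outcome defined by respiratory support. Gestational age is treated by the plan itself as a possible confounder. At stake are a somewhat wide confidence interval for the primary outcome and some power. In the follow-up comparisons after discharge, centre and assessor coincide, so any assessor differences stay in the error term.

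**Working it through.** **1. The plan's own figure.** Inputs from Sample size calculation: in the control group "40% developed moderate or severe BPD"; treatment is assumed to "reduce moderate or severe BPD (the primary endpoint) to 25% or less (number needed to treat, NNT = 5"; alpha 0.05 (taken as two-sided), power 80%; "the number of subjects per group will be *N* = 81", raised by 20% to 98 (81 × 1.2 = 97.2).

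n = [1.96√(2p̄(1−p̄)) + 0.842√(p₀(1−p₀) + p₁(1−p₁))]² / (p₀−p₁)²

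- 40% v 25%: (1.298 + 0.550)² / 0.0225 ≈ 152 per group. The stated 81 is not reproduced.
- 40% v 20%, the 20-point difference that an NNT of 5 implies: (1.270 + 0.532)² / 0.04 ≈ 81.2, that is 81 to 82. This matches.

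At 98 per group, power is about 61% for 40% v 25% and 87% for 40% v 20%. That mismatch is a separate matter. Here it means that the effect of stratifying has to be shown for both differences.

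**2. Standard error of the risk difference under the null.** Take equal-sized centres with mean rate 40%, 98 per arm, and set gestational age aside.

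- Unstratified SE = √(2 × 0.40 × 0.60 / 98) = 0.0700.
- True SD under stratified allocation = √(2 × [0.24 − V] / 98), where V is the variance of the centre rates.

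| Assumed centre rates | V | True SD | Unstratified SE | Critical value in true SDs | Real alpha |
|---|---|---|---|---|---|
| 40/40/40% | 0 | 0.0700 | 0.0700 | 1.960 | 5.0% |
| 30/40/50% | 0.0067 | 0.0690 | 0.0700 | 1.96 × 0.0700/0.0690 = 1.99 | 4.7% |
| 20/40/60% | 0.0267 | 0.0660 | 0.0700 | 1.96 × 0.0700/0.0660 = 2.08 | 3.8% |

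Simulation of 196 infants (blocks of 4 and a gestational-age log-odds effect of 0.8, both assumed; 2,000 trials each) agrees. SE v true SD is 0.0697 v 0.0683 at 30/40/50% and 0.0697 v 0.0658 at 20/40/60%; chi-square alpha is 4.4% and 3.6%.

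**3. Power at 40% v 25%.** Simulation with 98 per arm, six near-equal strata, a gestational-age log-odds difference of 0.6 (assumed) and 40,000 trials per scenario:

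| Assumed control rates by centre | Chi-square alpha | Chi-square power | Six-stratum CMH power | Gain (points) |
|---|---|---|---|---|
| no centre difference | – | 61.7% | 62.4% | 0.7 |
| 31/40/50% | – | – | – | about 1 |
| 27/39/54% | 4.2% | 62.1% | 64.7% | 2.6 |
| 23/39/58% | 3.7% | 62.7% | 66.7% | 4.0 |
| 20/39/62% | 3.1% | 62.9% | 68.8% | 5.9 |

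In the last three rows the stratified test held alpha at 5.0 to 5.1%. The 0.7 points in the first row come from gestational age alone. A repeat at 31/40/49% gave 1.5 points in all, 0.8 of them from gestational age; at 26/39/54% it gave 2.5, again with 0.8 from gestational age.

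**4. Power at 40% v 20%.** The same set-up gives gains of 0.7 (31/40/49%), 1.1 (26/39/54%) and 1.7 points (22/39/58%), from about 88%. A further run over growing centre spread gave about 0.2 to 2.4 points.

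**5. Logistic model.** At 20/40/60%, adding centre raises the printed SE of the log odds ratio under the null from 0.298 to 0.319. Under the 40% v 20% odds ratio, it moves the estimate from −0.903 to −1.011, and power rises from 81% to 84%. The statement that the SE is too large therefore fits the risk difference. For the log odds ratio it holds only relative to that estimator's own sampling SD (0.298 v 0.287).

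**The case against.** The strongest reply is that this is a condensed article, and that the way strata enter a model is commonly left to a statistical analysis plan. That stands for the logistic model: its covariate list is open, so centre is unnamed rather than excluded. It does not stand for the primary test, which the article positively fixes as an unstratified chi-square and which cannot take centre, nor for the t and Mann-Whitney tests.

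A reader might also infer more than the article supports:

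- **That power is certainly lost.** The loss arises only if rates differ between strata, and no centre rates are given. The larger gains need about a three-fold difference between centres (20% v 62%).
- **That the result would be invalid.** It would not. The error is conservative, with no excess of false positives and no bias in the risk difference.
- **That the whole gain is due to centre.** Part comes from gestational age, which the regression already names.
- **That assessor and centre coincide for the primary outcome.** The single-investigator statement concerns follow-up after discharge. The argument from local care applies at 36 weeks; the assessor argument does not expressly do so. Assessors are blinded and arms are balanced within centre, so assessor differences add noise, not bias. No size has been worked out for the two-year outcomes.
- **That six strata suit every outcome.** This is untested for rare events such as necrotizing enterocolitis or treated retinopathy, where the tables could be sparse.

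**Conclusion.** The point holds as one of efficiency. The design balances on six strata and the fixed primary test does not use them. If centres or gestational-age strata differ in outcome rate, that test is valid but conservative. Stratifying would then gain about 1 to 6 points of power at 40% v 25% and about 0.5 to 2.5 points at 40% v 20%, for assumed control rates from 31/40/50% to about 20/39/62%. If centres do not differ, the gain is close to zero. These figures rest on assumed centre rates, an assumed gestational-age effect and near-equal strata. No meaningful loss from stratifying appeared in any scenario examined. The change is worth making because it is nearly free and because power is only about 61% if the stated 40% v 25% is the real target.

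**What to change.** In Statistical analysis:

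1. Make the primary analysis a Cochran-Mantel-Haenszel test over the randomization strata, with the Mantel-Haenszel risk difference and its 95% CI. This keeps the scale on which the sample size was planned.
2. Name centre, with gestational age, as covariates in the logistic model and in the models for continuous and two-year outcomes.
3. Where a rank test is used, use a stratified one, such as the van Elteren test.
4. For rare outcomes, allow fewer strata or an exact method.

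The cost is wording and slightly more analysis complexity. Centre and stratum are already known for every infant, because allocation uses them. Settling this before unblinding also removes a later choice about whether to add centre.

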### Ethical and academic management

The research protocol was reviewed and approved by the Ethics Committee of Southwest Medical University, and we will not begin recruiting at other centers in the trial until local ethical approval has been obtained. The ethics committee will be responsible for supervising all procedures of the study. Prior to making any changes to the study protocol, a written application will be submitted to the ethics committee for approval, and new written informed consent will be obtained from the guardians.

An independent academic board, which is composed of competent department, data monitoring, and safety management advisors, has been implemented to oversee unwanted effects and risks, as well as the collection and management of the data. The academic board will review all research data every 3 months. Until the included patients are discharged, each potential adverse effect will be monitored and reported to the academic board within 48 h. All members of the academic board are independent of the sponsor and trial investigators and free of competing interests.

Participants, as well as the researchers, evaluators, doctors, and nurses who are responsible for screening, recruitment, dispensing medicine, and outcome assessment, will remain blinded to treatment allocations. The researchers conducting the statistical analysis will know only the group codes but not the corresponding interventions. When severe adverse effects occur, the academic board has the right to unseal emergency envelopes. The reason for unblinding and time will be recorded. We prepared an insurance policy for every participant. This will provide ancillary and posttrial care in the case of any harm resulting from participation in the clinical trial.

After consulting the academic board, the treatment will be suspended for the following conditions: (1) serious adverse reactions (death or severe infections) that occur during the testing or (2) a guardian request withdraw their infant from the study at any time and without any consequences. The primary outcome and other data collected for participants until the date of withdrawal will be used and analyzed as part of the ITT population.

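### The mid-term results go to the principal investigator with no stated purpose or rule, and the independent academic board has no stated role in the decision

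*Protocol article*

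**What the plan says.** The last paragraph of Statistical analysis in the protocol article sets the look and names who acts on it: "Mid-term data analysis will be conducted after inclusion of the first 98 patients", and then "The principal investigator will decide whether any measure should be taken in light of the results". It does not say whether the look concerns efficacy, futility, safety or sample size.

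Ethical and academic management describes an academic board that includes data-monitoring and safety advisors and is independent of the sponsor and the investigators. It says "The academic board will review all research data every 3 months". The board may open the emergency envelopes and is consulted before treatment is suspended. The same section keeps those who screen, recruit, dispense and assess outcomes blinded, and lets the analysts see coded groups only.

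Sample size calculation sets the error rate with the words "Adopting a maximum significance level of" 0.05 and mentions no interim look.

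**The concern.** Two things are at stake.

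**Bias.** Under Outcomes, the primary outcome requires survival to 36 weeks PMA without respiratory support and in room air. Under Use of cointervention, respiratory support follows each center's own practice. The endpoint therefore partly reflects decisions made at the bedside. If the person running the trial has seen the half-way difference, recruitment and respiratory care in the second half can shift, even without intent. An independent board exists to keep such knowledge away from the people conducting the trial.

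**Error rate.** The article presents 0.05 as a ceiling. A half-way comparison followed by an open-ended decision can raise the overall error above that ceiling, depending on what is tested and what the decision may be.

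**Working it through.** **1. Is any alpha reserved for the look?** Inputs from Sample size calculation: "40% developed moderate or severe BPD", 25% or less on hydrocortisone, a number needed to treat of 5, α = 0.05, power 80%, 81 per group. Sidedness is not stated; two-sided is assumed.

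- 40% against 25% needs 152 per group by the pooled normal formula, so 81 does not follow from the written rates.
- A number needed to treat of 5 means a difference of 1/5 = 20 points, that is 40% against 20%. This needs 82 (pooled) or 81 (arcsine).
- 81 × 1.2 = 97.2, rounded up to 98 per group, 196 in total.

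The 81 is thus reproduced by a single-look calculation that uses the whole 0.05, with no allowance for an interim test. The mismatch between 25% and a number needed to treat of 5 is a separate matter.

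**2. Type I error if both looks test the primary outcome at 0.05 and the trial may stop.** Information at the look is t = 98/196 = 0.5. Under no effect, the two test statistics are approximately bivariate normal with correlation √0.5 = 0.707.

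Overall error = 1 − P(|Z₁| ≤ 1.96 and |Z₂| ≤ 1.96) = 0.0831, about 8.3%.

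Simulating 1,000,000 trials with the chi-square test (49, then 98 per group, event rate 40% in both) also gives 8.3%. Counted against the 2 × 81 = 162 evaluable infants, t = 98/162 = 0.605 and the error is 7.9%.

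**3. Type I error if nothing is tested or changed on efficacy at the look.** Only the final test counts. The same simulation gives 4.9%.

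**4. Boundaries that hold 0.05 at t = 0.5 (two-sided nominal p).**

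| Rule | Mid-term | Final |
|---|---|---|
| O'Brien-Fleming | 0.0052 | 0.0480 |
| Haybittle-Peto | 0.001 | 0.0498 |
| Pocock | 0.0294 | 0.0294 |

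Haybittle-Peto with the final test left at 0.05 gives 5.02%, so strict control needs about 0.0498. These limits come from normal theory. In the chi-square simulation the O'Brien-Fleming limits gave 5.1%, because counts are discrete.

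**5. Cost in power, 98 per group, O'Brien-Fleming against a single final test (simulated).**

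- 40% against 25%: 61.6% falls to 61.1%.
- 40% against 20%: 87.3% falls to 87.0%.

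**6. Timing.** Infants are randomized at day 28 with gestational age 26+0 to 30+6, so they are then at 30+0 to 34+6 weeks PMA, which is 42 to 8 days before 36+0. Even accrual of 196 in one year is 196/365 = 0.537 per day. If the data were cut on the day the 98th infant entered, 0.537 × 8 = 4.3 to 0.537 × 42 = 22.6 infants would have no primary outcome yet. The ends of that range require all recent infants to be of the highest or the lowest eligible gestational age.

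**The case against.** Several stronger readings are tempting, and the document does not support them.

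- **That the plan breaks the 5% level.** No mid-term efficacy test or efficacy stop is named. A safety-only or futility-only look would not inflate the error. A boundary may also sit in an analysis plan or full protocol that is not shown, so its absence from a condensed article proves nothing. The 8.3% is conditional.
- **That the principal investigator may take any measure at will.** The sentence leaves open whether something is done; it does not license everything. Protocol changes also need approval from the ethics committee and new guardian consent.
- **That the board is bypassed.** It reviews the data every three months and is consulted before treatment is suspended. It has no stated role in this one decision, which is a narrower statement.
- **That the investigator will know which group received hydrocortisone.** Analysts work with codes and treating staff stay blinded. Under Randomization, the primary researcher keeps the full allocation list. If that person is also the principal investigator, the codes could be linked to treatments, but the text does not say so.
- **That the look will run on incomplete outcomes.** An analysis after inclusion of 98 infants may wait until their outcomes are in.

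These objections limit the size of the point but do not remove it. The article itself assigns the decision on the results to the principal investigator, and an unseen document could correct that only by contradicting it. Coding the groups hides the labels, not the existence or size of a half-way difference.

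**Conclusion.** The point stands as a badly fixed rule on who acts on the mid-term results: the principal investigator, with no stated purpose or rule, in a trial that already has an independent board. The risk of bias does not depend on any efficacy test. It needs only that the investigator sees the comparison. The size of that bias cannot be computed from the document.

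The effect on error is a range, not a demonstrated breach: near 5% with no efficacy test or data-driven change at mid-term, and about 8.3% with two unadjusted two-sided tests at 0.05 and freedom to stop (7.9% at 98 of 162). The timing figure of about 4 to 23 outstanding outcomes is secondary; it assumes even accrual and an immediate data cut.

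**What to change.** Replace the decision sentence in Statistical analysis with text that does the following.

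1. Sends the mid-term results, by group code, only to the existing independent academic board. The principal investigator receives only its recommendation to continue, modify or stop the trial.
2. States the purpose of the look. Either declare it safety-only with no efficacy test, leaving the final test at 0.05, or pre-specify a boundary: for example Haybittle-Peto (p < 0.001, final test at about 0.0498) or O'Brien-Fleming (0.0052, then 0.0480).
3. Runs the look once the first 98 infants have reached 36 weeks PMA.

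This takes a few sentences in the protocol, matching text in the board's working rules and no new committee. The power cost is nil for a safety-only look and about 0.5 point or less for O'Brien-Fleming. It has to be settled before the look, because knowledge of the half-way difference cannot be undone afterwards.
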